### 2.9. Sample Size and Randomization

The sample size was calculated to detect a 15% reduction in fasting triglycerides (SD 0.25 mmol/L), with α = 0.05, power ≥ 80%, and an anticipated dropout rate of 10%, resulting in a required total of 40 participants. Participants were randomly allocated to one of two treatment sequences (A followed by B, or B followed by A) using a computer-generated deterministic Wichmann–Hill-based algorithm. This approach ensured adequate randomization and strict allocation concealment, preventing any possibility of predicting the assignment.

### 2.10. Blinding

Both participants and the clinical research team were blinded to treatment allocation throughout the trial. The capsules containing omega-3 (oil extracted from 1 g of *Nannochloropsis* sp. microalga, providing 250 mg of eicosapentaenoic acid) and the control (high-oleic sunflower oil, HOSO) were identical in size, shape, color, weight, and packaging, and labeled only with the participant code and study phase. This ensured that neither participants nor the research team involved in recruitment, assessments, or sample collection could identify the intervention. The trial statistician was also blinded to capsule coding. Only the principal investigator had access to the randomization key, which was securely stored and not opened until all data were collected, the database was locked, and the statistical analysis performed.

### 2.11. Statistical Analyses

We presented continuous variables with normal distributions as means and standard deviations, continuous variables with non-normal distributions as medians and interquartile ranges (1st–3rd quartiles), and categorical variables as proportions. Differences between participants in different groups (women/men) were assessed using *t*-tests for normally distributed continuous variables, Mann–Whitney U tests for non-normally distributed continuous variables, and chi-squared tests for categorical variables. Associations among continuous variables were studied using Spearman’s rank correlations adjusted for multiple comparisons using the Bonferroni correction. For the crossover analyses, a linear mixed-effects model (LMM) was used to evaluate treatment effects, including fixed effects for treatment period and sequence, and a random intercept for participant to account for within-subject variability. Baseline triglyceride values at the beginning of each period were included as covariates. Potential carryover effects were examined through the sequence term and further tested by including a first-order carryover variable in sensitivity analyses If statistically significant carryover is observed (*p* < 0.05), a period-1-only sensitivity analysis will be reported. The protocol already incorporates a 10-week washout period, designed to minimize residual EPA incorporation. Analyses were conducted in R (version 4.3.1).

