## 3. Results

The CONSORT flow diagram (Figure 2) summarizes participant progression through the RIO-Study, from initial registration of interest to the completion of the follow-up phase. A total of 406 individuals initially expressed interest in participating in the trial, of whom 132 attended the in-person informed consent session. A total of 119 individuals provided signed informed consent. Screening assessments were performed with 112 participants, resulting in the enrolment of 40 eligible individuals who met all inclusion criteria and proceeded to Visit 1.

Baseline analysis of RIO-Study participants revealed a cardiometabolic risk profile characterized by excess adiposity, moderate dyslipidemia, and low physical activity in a considerable proportion of the cohort. The mean age was 40.6 ± 11.6 years, with no significant differences between sexes. However, men exhibited greater waist circumference and waist-to-hip ratio (100 ± 10.8 vs. 91.6 ± 11.9 cm; *p* < 0.001), higher systolic blood pressure (130 ± 12.0 vs. 122 ± 13.4 mmHg; *p* = 0.001), and higher levels of vigorous physical activity (2.40 [0.00;9.00] vs. 0.00 [0.00;0.36] (METs·min/week); *p* < 0.001), whereas women presented a higher proportion of normal-weight individuals (0% vs. 13%; *p* < 0.001), higher body fat percentage (31.1 ± 5.30 vs. 39.7 ± 4.75%; *p* < 0.001), and less daily sitting time (8.10 ± 2.28 vs. 6.83 ± 2.27 h; *p* = 0.006) (Table 1).

Regarding lipid profile (Table 2), no significant sex differences were observed in Apo-B, total cholesterol, low-density lipoprotein cholesterol (LDL-C), or non-high-density lipoprotein cholesterol (HDL-C). Nevertheless, men had significantly higher triglyceride levels (168 ± 84.7 mg/dL vs. 122 ± 64.9 mg/dL, *p* = 0.004), VLDL-C concentrations (33.7 ± 17.2 mg/dL vs. 24.4 ± 13.0 mg/dL, *p* = 0.004), and atherogenic index values (4.28 ± 1.22 vs. 3.59 ± 0.92, *p* = 0.002) compared to women. Conversely, women exhibited higher HDL-C levels (56.6 ± 13.3 mg/dL vs. 46.9 ± 9.39 mg/dL, *p* < 0.001). These differences indicate a less favorable lipid phenotype in men, characterized by elevated triglyceride-rich lipoproteins and reduced HDL-C concentrations, potentially contributing to higher cardiometabolic risk.

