Correlation analysis (Figure 3) showed consistent patterns among anthropometric measures, body composition, and lipid profile parameters. Adiposity markers (BMI, waist circumference, fat mass) were strongly and positively correlated with each other and inversely correlated with HDL-C, while lean mass showed near-perfect correlations with total and compartmental body water. Apo-B, LDL-C, and total cholesterol formed a highly interrelated lipid cluster, with LDL-C and non-HDL-C displaying near-perfect collinearity. Moderate-to-vigorous physical activity was inversely associated with body fat percentage and triglyceride levels.

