Correlation analyses demonstrated strong positive associations between adiposity markers and triglycerides, and inverse associations between moderate-to-vigorous physical activity, body fat percentage, and triglycerides. Nearly half of participants failed to meet WHO physical activity recommendations, underscoring a significant behavioral and public health gap. These results reinforce the role of physical activity as a modifiable determinant of cardiometabolic risk [27,28].

The findings are consistent with national data from the Chilean National Health Survey 2016–2017, which reported overweight/obesity in 74.2% of adults and hypertriglyceridemia in 35.8% of adults [29]. The high prevalence of abdominal obesity, particularly in women, mirrors regional data linking this phenotype to insulin resistance and metabolic syndrome [30], enhancing the representativeness of the study population. These baseline results provide a robust foundation to assess the impact of nutritional-dose omega-3 supplementation, which has been shown in other cohorts to lower triglycerides, modulate lipid metabolism-related gene expression, and reduce inflammatory biomarkers [20,21,31]. The integration of molecular and functional endpoints in subsequent phases will clarify interindividual variability in response and support the development of personalized nutrition strategies in Latin America.

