**Figure 3 nutrients-17-03397-f003:**
[figure not shown]
Correlation heatmap displaying the relationships between anthropometric, metabolic, and physical activity variables. The color scale represents the strength and direction of the correlations (blue for positive and red for negative correlations). Only statistically significant correlations are shown. Multiple comparisons were adjusted using the Bonferroni correction.

**Table 1 nutrients-17-03397-t001:** Baseline anthropometric, body composition, hemodynamic, and physical activity characteristics of participants by sex. Values are mean (SD) or median [Q1; Q3].

	SCR-All	SCR-Men	SCR-Women	*p*-Value
Age (years), mean (SD)	40.6 (11.6)	38.2 (11.8)	42.1 (11.2)	0.085
Body mass index (kg/m^2^), mean (SD)	30.8 (5.01)	31.0 (4.37)	30.7 (5.40)	0.712
BMI categories:				0.05
≤25 kg/m^2^ (*n*, %)	9 (8.04%)	0 (0.00%)	9 (13.0%)	
25.0–29.9 kg/m^2^ (*n*, %)	51 (45.5%)	22 (51.2%)	29 (42.0%)	
30.0–39.9 kg/m^2^ (*n*, %)	44 (39.3%)	19 (44.2%)	25 (36.2%)	
≥40 kg/m^2^ (*n*, %)	8 (7.14%)	2 (4.65%)	6 (8.70%)	
Waist circumference (cm)	95.0 (12.2)	100 (10.8)	91.6 (11.9)	<0.001
Abdominal obesity (*n*, %)	62 (55.4%)	19 (44.2%)	43 (62.3%)	0.093
Hip circumference (cm)	107 (8.75)	107 (7.34)	108 (9.55)	0.624
Waist-to-hip ratio	0.94 (0.08)	0.99 (0.08)	0.92 (0.07)	<0.001
Systolic blood pressure (mmHg), mean (SD)	125 (13.5)	130 (12.0)	122 (13.4)	0.001
Diastolic blood pressure (mmHg), mean (SD)	77.4 (9.78)	79.5 (9.93)	76.2 (9.53)	0.085
Heart rate (bpm), mean (SD)	69.6 (9.15)	66.3 (8.43)	71.6 (9.05)	0.002
Smokers (*n*, %)	35 (31.2%)	17 (39.5%)	18 (26.1%)	0.199
Physical activity: walking (METs·min/week), median [Q1; Q3]	231 [0.00; 462]	214 [0.00; 487]	240 [0.00; 462]	0.962
Moderate physical activity (METs·min/week), median [Q1; Q3]	240 [1.23; 520]	180 [0.00; 520]	300 [3.08; 520]	0.185
Vigorous physical activity (METs·min/week), median [Q1; Q3]	0.00 [0.00; 440]	2.40 [0.00; 9.00]	0.00 [0.00; 0.36]	<0.001
Sitting time (hours/day), mean (SD)	7.31 (2.35)	8.10 (2.28)	6.83 (2.27)	0.006
Lean mass (kg), mean (SD)	52.9 (10.8)	63.0 (8.99)	46.6 (5.84)	<0.001
Fat percentage (%), mean (SD)	36.4 (6.47)	31.1 (5.30)	39.7 (4.75)	<0.001
Basal metabolic rate (kcal/day), mean (SD)	1372 (224)	1579 (203)	1243 (113)	<0.001

SCR, screening; SD, standard deviation; BMI, body mass index; MET, metabolic equivalent task.

**Table 2 nutrients-17-03397-t002:** Baseline lipid profile and apolipoproteins of the study population (*n* = 112).

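### The correlations in Section 2.11 and Figure 3 are not adjusted for sex; for traits that differ strongly between men and women, pooling partly restates the sex difference and can cancel within-sex associations

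*Protocol article*

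**What the plan says.** Section 2.11 gives the whole method: "Associations among continuous variables were studied using Spearman’s rank correlations adjusted for multiple comparisons using the Bonferroni correction". Multiplicity is the only adjustment named. Figure 3 is a single display, "Correlation heatmap displaying the relationships between anthropometric, metabolic, and physical activity variables"; its caption mentions no covariate and no split by sex, and says that non-significant cells are left out. The sample is everyone screened: "Screening assessments were performed with 112 participants".

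The same paragraph of Section 2.11 plans a comparison of women and men on each variable, and Tables 1 and 2 report it. Several gaps are large, for example "Lean mass (kg), mean (SD) 52.9 (10.8) 63.0 (8.99) 46.6 (5.84) <0.001" (columns: all, men, women, p-value).

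Section 3 then reports: "Moderate-to-vigorous physical activity was inversely associated with body fat percentage and triglyceride levels". Section 4 concludes: "These results reinforce the role of physical activity as a modifiable determinant of cardiometabolic risk".

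**The concern.** When two traits both differ by sex, their correlation in a mixed sample has two parts: the association within each sex, and a part that comes only from the distance between the male and female means. Bonferroni controls the number of false positives over many tests. It does not remove the second part.

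Two things are at stake for the article's second aim, the baseline cardiometabolic profile. Some cells of the heatmap may largely repeat the sex comparisons already in Tables 1 and 2. Others may be blank because the two parts cancel: women have more body fat than men but higher HDL-C, lower triglycerides and a smaller waist. The Discussion also moves from description to physical activity as something that can be changed to lower risk, and that reading needs an association not produced by a fixed trait.

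**Working it through.** **Inputs.** Men and women from the BMI categories in Table 1: 0+22+19+2 = 43 and 9+29+25+6 = 69, so the share of men is p = 43/112 = 0.384 and p(1-p) = 0.2365. Means (SD), men vs women, and SD for all, from Tables 1 and 2:

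| Trait | Men | Women | SD, all |
|---|---|---|---|
| Fat % | 31.1 (5.30) | 39.7 (4.75) | 6.47 |
| Lean mass, kg | 63.0 (8.99) | 46.6 (5.84) | 10.8 |
| Waist, cm | 100 (10.8) | 91.6 (11.9) | 12.2 |
| HDL-C, mg/dL | 46.9 (9.39) | 56.6 (13.3) | 12.8 |
| Triglycerides, mg/dL | 168 (84.7) | 122 (64.9) | 76.2 |
| BMI, kg/m² | 31.0 (4.37) | 30.7 (5.40) | 5.01 |

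**Step 1: reproduce the article's pooled figures.** For fat %, the within-sex sum of squares is 42×5.30² + 68×4.75² = 2714. The between-sex sum is (43×69/112)×8.6² = 1959. The pooled SD is √[(2714+1959)/111] = 6.49, against 6.47 in Table 1. The same sum gives 10.75 for lean mass (10.8), 12.8 for HDL-C (12.8) and 76.2 for triglycerides (76.2). The columns are consistent. Sex accounts for 1959/4673 = 42% of the variation in fat % and 7125/12839 = 55% of that in lean mass.

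**Step 2: correlation from sex mix alone.** With zero correlation within each sex, r = p(1-p) × (gap in X) × (gap in Y) / (SD_X × SD_Y). For lean mass and fat %: 0.2365 × 16.4 × (-8.6) / (10.8 × 6.47) = -0.48.

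The other pairs follow in the same way. They were also simulated: 43 men and 69 women, tabulated means and SDs, normal traits, log-normal triglycerides, 4,000 samples per pair. The number of tests behind the Bonferroni correction is not stated, so families of 45, 190 and 300 tests are assumed.

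| Pair | r by formula | Mean pooled Spearman | Pooled rejection at 45 / 190 / 300 tests |
|---|---|---|---|
| Lean mass, fat % | -0.48 | -0.48 | 99% / 98% / 97% |
| Lean mass, HDL-C | -0.27 | -0.28 | 39% / 25% / 21% |
| Fat %, HDL-C | +0.24 | +0.25 | 25% / 14% / 12% |
| Fat %, waist | -0.22 | -0.22 | 17% / 9% / 7% |
| Fat %, triglycerides | -0.19 | -0.20 | 13% / 7% / 5% |
| Waist, HDL-C | -0.12 | -0.13 | 3% / 1% / 0.7% |
| BMI, HDL-C | -0.01 | -0.01 | 0.2% or less |

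The rank correlation adjusted for sex rejected at about the nominal rate in every row (0.3% or less at these thresholds; about 5% at an unadjusted 5% level). For LDL-C with total cholesterol the formula gives 0.00.

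**Step 3: cancellation.** Here a within-sex correlation is assumed, because the article gives none.

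| Pair | Assumed within-sex r | Mean pooled Spearman | Power at 5%, pooled vs adjusted |
|---|---|---|---|
| Fat %, HDL-C | -0.3 | +0.05 | 7% vs about 86% |
| Fat %, triglycerides | +0.3 | 0.00 | 4% vs 86% |
| Fat %, waist | +0.3 | -0.02 | 4% vs 86% |

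At 190 tests even the adjusted analysis finds a correlation of 0.3 only about a quarter of the time. At 0.4 it finds fat % with triglycerides in 68% of samples, against 0.1% pooled.

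**Step 4: the activity statements.** Section 3 speaks of moderate-to-vigorous activity. Table 1 gives no sex comparison for that combined variable, only for its parts:

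- Moderate activity has medians of 180 in men and 300 in women (p = 0.185).
- Vigorous activity is higher in men (p < 0.001), but its row mixes scales: 0.00 [0.00; 440] for all against 2.40 [0.00; 9.00] for men and 0.00 [0.00; 0.36] for women.

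The size of the sex contribution to activity/fat % therefore cannot be computed. Only directions can be given. The vigorous-activity gap (higher in men) with the fat % gap (lower in men) pushes towards the reported inverse sign. With the triglyceride gap (higher in men) it pushes against the reported sign.

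**The case against.** The strongest reply is that a pooled correlation answers a legitimate question about adults screened in Valdivia, and its test is valid for that question. This stands. A non-zero coefficient caused by sex mix is a true feature of the mixed sample, not a type I error, and the rejection rates above should be read in that light.

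The largest distortions also fall on pairs that the text of Section 3 does not name. It names BMI, waist and fat mass as inversely related to HDL-C:

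- For BMI the distortion is nil, and for waist it is slight.
- For fat mass, a rough figure from the mean lean mass and fat % is 63.0×0.311/0.689 = 28 kg in men and 46.6×0.397/0.603 = 31 kg in women. This small gap works against the reported sign.

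The cancellation rests on assumed within-sex correlations, and Section 4 reports positive associations of adiposity markers with triglycerides, so pooling has not hidden that relation in general. All of this narrows the point.

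A reader might infer that the activity/body-fat association is a product of sex mix. The documents do not support that. The combined variable has no reported sex gap, and its moderate part leans the other way. Even with assumed vigorous-activity gaps, sex mix alone gives only -0.05 to -0.20, while the critical value at n = 112 is 0.304 to 0.356 for 45 to 435 tests. Sex may inflate this association but would rarely create a significant cell by itself.

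Finally, Figure 3 could not be seen, and the absence of adjustment is read from the methods sentence and the caption. But the analysis is reported as done, with its one adjustment named, so it is not a detail deferred to another document.

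**Conclusion.** The point holds in a limited form. As described, the correlations do not separate the within-sex relation from the sex gap. This matters for pairs in which both traits differ strongly by sex, chiefly those involving lean mass and fat percentage: up to about -0.48 from sex mix alone, and moderate within-sex associations of fat % with HDL-C, triglycerides or waist cancelled to about zero. It matters little for waist/HDL-C and not at all for BMI pairs or the Apo-B/LDL-C/total cholesterol cluster.

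For activity/body fat, inflation by sex is possible but its size is unknown. For activity/triglycerides, the only clear sex gap works against the reported direction, so sex mix does not explain that result.

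The figures rest on the tabulated means and SDs, the distribution shapes used in the simulation, assumed Bonferroni families and, for the cancellation, assumed within-sex correlations. The point concerns the article's second aim only. The randomized comparison of fasting triglycerides is not affected.

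**What to change.** In Section 2.11 and Figure 3, report partial Spearman correlations adjusted for sex, or separate heatmaps for men and women, beside the pooled coefficients. Keep the Bonferroni correction and state the number of tests it covers. Label the pooled coefficients as a description of the mixed sample. In Section 4, rest the sentence on physical activity as a modifiable determinant on the sex-adjusted results, and soften it if they do not hold.

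The cost is one re-run on data already held, one degree of freedom (110 to 109), and edits to one figure and its text. Some reported cells may weaken and others may appear.

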## 2. Materials and Methods

### 2.1. Trial Design

The RIO-Study (Response to an Intervention with Omega-3 Fatty Acids on Lipid and Inflammatory Profiles in Overweight and Obese Individuals with Hypertriglyceridemia in Valdivia, Chile) is a randomized, double-blind, placebo-controlled, two-period, two-sequence crossover trial. Each participant completed two supplementation phases of six weeks, separated by a 10-week washout period to minimize carryover effects (Figure 1). Recruitment was conducted between July 2024 and June 2025 at Universidad San Sebastián, Valdivia, Chile. This study was initially approved by the Scientific Ethics Committee of Universidad San Sebastián (CEC-USS, No. 42-24, 11 April 2024). Subsequently, the Scientific Ethics Committee of the Los Ríos Health Service (No. 186, 12 June 2024) provided oversight of protocol amendments, which, in accordance with its procedures, were reported collectively upon study completion.

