### 2.5. Aims

The primary aim of this trial is to determine the effectiveness of omega-3 fatty acids at nutritional doses in improving fasting serum triglyceride levels. Secondary aims include postprandial serum triglyceride levels (0, 2, 4, and 6 h); the expression of lipid metabolism genes, such as peroxisome proliferator-activated receptor alpha (PPARα) and sterol regulatory element-binding transcription factor 1 (SREBP1c isoform), in peripheral blood mononuclear cells (PBMCs) during fasting and 4 h after eating; plasma concentrations of low-grade inflammatory markers, including tumor necrosis factor alpha (TNFα) and interleukin-6 (IL-6), assessed at fasting and 4 h postprandial; and the atherogenic properties of very-low-density lipoproteins (VLDLs) in the fasting state, including their relative richness in triglycerides, remnant cholesterol, apolipoprotein C-I, and apolipoprotein C-III, in individuals from the Chilean population.

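### A single period-baseline term in the random-intercept model gives less precision than a split baseline and, depending on correlations the protocol does not give, can do worse than no baseline

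*Protocol article*

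**What the plan says.** Section 2.1 describes a "two-period, two-sequence crossover trial" with "two supplementation phases of six weeks, separated by a 10-week washout period". The primary aim (section 2.5) is "improving fasting serum triglyceride levels". Section 2.11 analyses the crossover with a linear mixed model that has fixed effects for treatment, period and sequence and "a random intercept for participant to account for within-subject variability". It adds: "Baseline triglyceride values at the beginning of each period were included as covariates". In data with one row per participant and period, the natural reading is one covariate that takes the V1 value in period 1 and the V3 value in period 2. The sentence also allows the V1 and V3 values as two separate terms. No correlation between visits is given anywhere in the article.

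**The concern.** In a 2×2 crossover the treatment effect is estimated from each person's difference between periods. A baseline covariate helps only as far as the V1-V3 difference predicts the V2-V4 difference, which is the within-person slope. The between-person slope is much steeper, because a person with high triglycerides is high at every visit. A random-intercept fit with one baseline term returns a blend of the two slopes. If the blend is too steep for the within-person relation, the model subtracts noisy baseline differences from the treatment contrast.

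At stake is precision on the primary endpoint in a trial of 40. There is a secondary issue of bias: a residual treatment effect at V3 that has gone by V4 would enter the treatment estimate through the same slope.

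**Working it through.** **Inputs.** Section 2.9 plans to "detect a 15% reduction in fasting triglycerides" with SD 0.25 mmol/L, "with α = 0.05" and power of at least 80%. It states "an anticipated dropout rate of 10" per cent and a total of 40, so 40 × 0.9 = 36 completers, taken as 18 per sequence. Same-period measurements are 6 weeks apart and the others 10 to 22 weeks apart (section 2.1). All correlations below are assumptions.

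**The plan's own figure.** The article does not give the mean to which the 15% applies. With the screening mean of 140 mg/dL (Table 2; 1.58 mmol/L) the difference is 0.237 mmol/L. The two-sample formula gives 2 × (1.96 + 0.84)² × 0.25² / 0.237² = 17.4, so 18 per group and 36 in all, and 36/0.9 = 40. The stated 40 is reproduced under that assumed mean.

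**Formula.** Let dX be a participant's difference between the two baselines and dY the difference between the two outcomes. With slope b, the treatment contrast has variance proportional to

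var(dY) − 2b·cov(dX,dY) + b²·var(dX).

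The within-person slope is w = cov(dX,dY)/var(dX). With var(dX) = var(dY), the ratio to no baseline is 1 − 2bw + b². It exceeds 1 only if b > 2w. A split baseline uses b = w, apart from estimation error.

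**Simulation.** REML fits, 36 completers, 1,500 replicates, unit SD. b is the fitted single slope. The variance ratio of one term to split is the squared ratio of the simulated SDs of the treatment estimate. CI ratios are mean 95% interval widths relative to no baseline.

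| Assumed correlations | w | b | 1 − 2bw + b² | Variance, one term / split | CI, one term / none | CI, split / none |
|---|---|---|---|---|---|---|
| all 0.3 | 0 | 0.26 | 1.07 | (0.203/0.197)² = 1.06 | 1.03 | 1.01 |
| all 0.5 | 0 | 0.43 | 1.18 | (0.182/0.166)² = 1.20 | 1.09 | 1.01 |
| all 0.6 | 0 | 0.54 | 1.29 | (0.169/0.148)² = 1.30 | 1.13 | 1.01 |
| all 0.7 | 0 | 0.65 | 1.42 | (0.154/0.128)² = 1.45 | 1.18 | 1.01 |
| decay 0.75, 0.72, 0.70, 0.68 | 0.17 | 0.72 | 1.27 | (0.146/0.127)² = 1.32 | 1.11 | 1.00 |
| same period 0.70, others 0.6 | 0.25 | 0.67 | 1.11 | (0.157/0.144)² = 1.19 | 1.04 | 0.98 |
| same period 0.75, others 0.6 | 0.375 | 0.73 | 0.99 | (0.147/0.138)² = 1.13 | 0.98 | 0.93 |
| same period 0.80, others 0.6 | 0.50 | 0.78 | 0.83 | (0.135/0.129)² = 1.10 | 0.89 | 0.86 |
| same period 0.60, others 0.4 | 0.33 | 0.58 | 0.95 | (0.177/0.172)² = 1.06 | 0.96 | 0.94 |

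The variance ratios carry simulation error of a few percentage points: separate runs at equal correlation 0.6 gave 22%, 26% and 30% against the split. The closed form and the simulation agree in direction. With cross-period correlations of 0.6, the single term breaks even with no baseline at a same-period correlation between 0.70 and 0.75. Coverage of the single-term model was 0.948-0.953 throughout; none of these runs included carryover.

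**Two participant-level terms.** V1 and V3 entered as separate terms are the same in both of a participant's rows, so with complete data they cancel from the period difference and leave the treatment estimate as it is with no baseline. The simulated interval ratio was 0.994-0.999 under equal correlations. It was lower in other scenarios, but since the estimate itself is unchanged, that is not a real gain.

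**Carryover at V3 only.** If V3 is lower by c after omega-3 and the effect has gone by V4, the single-term estimate shifts by −b·c/2. With c = 0.3 SD and b = 0.54 this is −0.54 × 0.3/2 = −0.08 SD, in favour of omega-3; simulation gave the same. The split shifts by −w·c/2, which is zero when w = 0. With w = 0.50 and b = 0.78 the shifts are −0.075 (split) and −0.117 (single), so the split then reduces the problem but does not remove it.

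**Scale.** A 26% variance penalty corresponds to 36 × (1 − 1/1.26) ≈ 7 completers. For power, take 0.25 as the per-measurement within-person SD, so SE = 0.25 × √2/√36 = 0.0589. At 140 mg/dL with a 30% wider interval, 0.237/(1.3 × 0.0589) − 1.96 = 1.13, which is about 87%. At the eligibility floor of 100 mg/dL (difference 0.169 mmol/L), power goes from about 82% to about 72% with a 13% wider interval.

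**The case against.** The strongest objection is that the loss against no baseline is conditional. A reader might infer that the planned adjustment always widens the interval beyond using no baseline. The documents do not support that: they give no correlations, and the ratio falls below 1 once the same-period correlation clearly exceeds the cross-period one. With visits 6 weeks apart within a period and 10 to 22 weeks apart otherwise, some decay is plausible. This stands. What survives is the comparison with the split, which was better on average in every scenario run.

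Second, the plural wording may mean two participant-level terms, and a condensed article may leave the coding to a fuller document. This also stands in part, and the absence of that detail is not the complaint. But the two-term reading gives up whatever within-person information the baselines hold, so the split is the better specification under either reading.

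Third, the practical effect may be small. Without carryover there is no bias and coverage is nominal, and under the 140 mg/dL assumption planned power survives even a 30% wider interval. A reader might infer an underpowered or invalid primary analysis; neither follows.

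Fourth, section 2.11 already plans a carryover term and a period-1-only analysis, after a 10-week washout. These are sensitivity analyses, and they leave the slope in the main model as it is. Section 4 accepts that residual carryover cannot be fully excluded.

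Finally, a reader might infer that baseline triglycerides will be the covariate for TNFα, IL-6, gene expression or VLDL composition. Section 2.11 does not say so; the sentence fits the primary endpoint.

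**Conclusion.** The point holds in conditional form. With one time-varying baseline term, the treatment variance is about 6-32% above that of a split baseline across the range considered. It is higher still if all correlations are equal and 0.7 or more (45% at 0.7 in the table). Whether the single term is worse than no baseline depends on whether the fitted slope exceeds twice the within-person slope, and the article gives nothing from which to judge that. Carryover confined to V3 would add a shift of −b·c/2, about −0.08 SD in the example.

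The figures rest on 36 completers, normal data, equal variances and assumed correlations. This is an avoidable loss of efficiency and does not make the analysis invalid.

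**What to change.** Prespecify two baseline terms in place of one: the participant's mean of the V1 and V3 values, and the period baseline minus that mean. Equivalently, with complete data, regress the within-person outcome difference on the baseline difference and sequence. Where the model is applied to secondary outcomes, use each outcome's own baseline and say so.

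The cost is one degree of freedom. If the within-person slope is truly zero, the variance rises by up to about 3-6% against no adjustment (interval about 1% wider in the table). No new data are needed. Section 2.8 describes the trial assays as still to be done, and section 2.10 keeps the randomization key closed until the analysis has been performed, so the change can be fixed while blinded.

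### Showing the period-1-only analysis only after a carryover test with p < 0.05 makes it a selectively reported and often misleading companion to the crossover result

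*Protocol article*

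**What the plan says.** Section 2.1 of the protocol article describes a "randomized, double-blind, placebo-controlled, two-period, two-sequence crossover trial", with the two phases "separated by a 10-week washout period to minimize carryover effects".

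Section 2.11 sets the crossover analysis: "a linear mixed-effects model (LMM) was used to evaluate treatment effects, including fixed effects for treatment period and sequence", plus a random intercept for participant. It adds: "Baseline triglyceride values at the beginning of each period were included as covariates". On carryover it says: "Potential carryover effects were examined through the sequence term and further tested by including a first-order carryover variable in sensitivity analyses". The rule at issue follows: if the carryover test gives p < 0.05, "a period-1-only sensitivity analysis will be reported".

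No period-1 analysis is planned in the article under any other condition. The triggered analysis is called a sensitivity analysis, and nothing says that it takes the place of the mixed model.

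**The concern.** In a two-by-two crossover the carryover test compares the sequences on the average of both periods. Half of that average is the period-1 outcome, and in period 1 the sequence groups are the treatment groups. If one sequence happens to draw participants with higher triglycerides, the carryover test tends to reject and the period-1 comparison tends to show a treatment difference, for the same reason. A rule that shows period 1 only after rejection selects those datasets.

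What is at stake is how the primary endpoint, fasting triglycerides, is read. Once a report has declared carryover significant, a period-1 estimate printed beside the crossover estimate invites the reader to prefer it. Its p-value and confidence interval are then no longer what they claim to be. The sensitivity label does not remove that selection.

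**Working it through.** **Inputs from the article.** Two periods and two sequences (section 2.1). Sequence term as the carryover test, p < 0.05 as the trigger, and period baselines as covariates (section 2.11). Forty participants with 10% anticipated dropout (section 2.9), so 40 × 0.9 = 36, or 18 per sequence if the sequences are equal.

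**Assumptions.** The within-subject correlation ρ of triglycerides is not given, so a range is used, with equal correlation between all measurements. Tests are two-sided at 5%. There is no treatment effect and no carryover unless stated. The treatment term is taken to be in the model. With treatment, period and sequence fitted, a first-order carryover term is aliased with sequence, so the further test supplies no separate trigger.

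**Step 1. Without baselines.** Take outcome variance 1 in each period.
- Variance of a participant's two-period mean: (1+ρ)/2.
- Covariance of that mean with the period-1 outcome: (1+ρ)/2.
- Correlation between the sequence and period-1 contrasts: r = √((1+ρ)/2).

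The wanted probability is P(|Z₁| > 1.96 given |Zₛ| > 1.96) for a bivariate normal pair with correlation r:

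| ρ | r | Period 1 falsely significant, given the trigger |
|---|---|---|
| 0.3 | 0.806 | 45% |
| 0.5 | 0.866 | 53% |
| 0.7 | 0.922 | 64% |
| 0.8 | 0.949 | 71% |
| 0.9 | 0.975 | 79% |

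**Step 2. With baselines, as section 2.11 plans.** Let period 1 be analysed by ANCOVA on its baseline, and let the sequence test be a between-participant regression of mean outcome on sequence and mean baseline.
- Residual variance in period 1: 1−ρ².
- Residual variance of the adjusted mean: (1−ρ)(1+3ρ)/(2(1+ρ)). The covariance of the two residuals has the same value.
- Hence r = √((1+3ρ)/(2(1+ρ)²)), which is 0.749 at ρ = 0.4, 0.732 at 0.7 and 0.724 at 0.8.
- The conditional error from the same bivariate normal calculation is 38%, 36% and 35%.

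That is a large-sample figure. Simulation with 18 per sequence and estimated coefficients gave 33-37% for ρ = 0.5-0.9, and repeat runs over ρ = 0.4-0.8 agree to within a few points. I use roughly 31-37%.

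**Step 3. The same test without the gate.** In those simulations the period-1 test had 4.8-5.1% error when reported in every trial. The excess comes from the gate and not from the period-1 analysis.

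**Step 4. How often.** The trigger fires in about 5% of these trials, all of them false alarms. Then 0.05 × 0.31 = 1.6% and 0.05 × 0.37 = 1.9%, so about 1.5-2% of null trials show a triggered, falsely significant period-1 result. At ρ = 0.7 the mean absolute spurious period-1 effect in triggered trials is about 0.41 SD with baseline adjustment and 0.70 SD without. The crossover estimate in triggered trials keeps about 5% error.

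**Step 5. If carryover is real** (ρ = 0.7, no treatment effect; the adjusted runs assume equal carryover in the period-2 baseline and outcome):

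| Carryover | Model | Trigger fires | Period-1 error, given the trigger | Crossover error, all trials |
|---|---|---|---|---|
| 0.3 SD | unadjusted | 7.5% | 38% | 20% |
| 0.3 SD | adjusted | 5.0% | 34% | 20% |
| 0.6 SD | unadjusted | 15.8% | 17% | 62% |
| 0.6 SD | adjusted | 5.7% | 28% | 55% |

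At 0.6 SD the crossover estimate is the worse of the two, yet the gate would still withhold period 1 in 84% (unadjusted) to 94% (adjusted) of trials.

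**The case against.** The best defence is that this is not the classical two-stage procedure, in which the carryover test chooses the primary estimator. The mixed model stays in place and period 1 is only an addition. That stands. A reader might infer that the type I error of the primary analysis is inflated, but section 2.11 does not support this.

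Four further limits also stand.
- The unadjusted 45-79% overstates the case for this trial, because section 2.11 includes period baselines. The figures near one third are the relevant ones.
- The event is uncommon, at about 1.5-2% of null trials.
- The trigger is two-sided and selects imbalances in both directions. With no carryover it does not favour omega-3.
- One might say that the rule shows period 1 in exactly the datasets where it misleads, beside a valid crossover estimate. That holds only if true carryover is absent. The article relies on a 10-week washout but concedes in its limitations that carryover cannot be excluded, and with large carryover period 1 may be the less misleading result.

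The last limit argues against the gate and not for it: if period 1 is useful under carryover, it should not depend on a test that seldom detects carryover.

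Two smaller points. Period 1 could have closer to 20 per group than 18, since participants lost after the first phase still contribute; the correlations in Steps 1 and 2 do not depend on that number. And the article does not say outright that period 1 is withheld when the test is not significant, but a conditional sentence with a stated threshold is naturally read that way.

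**Conclusion.** The point holds in limited form. The p < 0.05 gate in section 2.11 is a stated rule, and it creates a selection effect that unconditional reporting would not have. In trials with no carryover and no treatment effect, the baseline-adjusted period-1 test is falsely significant in roughly 31-37% of the trials where it is shown, against 5% nominal, and in about 1.5-2% of all such trials. These figures rest on assumed within-subject correlations of 0.4-0.8, equal correlation between measurements and 18 per sequence.

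The primary mixed model keeps its nominal error in that setting. The damage is a misleading companion result, which may draw readers away from the primary estimate. It is worth correcting because the fix is so cheap, but it is not a flaw in the primary analysis.

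**What to change.** In section 2.11, delete the p < 0.05 condition. State that the two-period mixed model is the basis for inference whatever the carryover test shows. Then either report the baseline-adjusted period-1 estimate with its confidence interval in every case, labelled descriptive, or omit it.

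Optionally, describe residual carryover by the between-sequence difference in V3 minus V1 fasting triglycerides, with a confidence interval.

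The cost is one sentence and, if period 1 is kept, one extra descriptive estimate in the report. No new data are needed.
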